## Abstract

**Background:**

Stress urinary incontinence is a common condition affecting approximately 20% of adult women causing substantial individual (quality of life) and economic (119 million Euro/year spent on incontinence pads in the Netherlands) burden. Pelvic floor muscle training (PFMT) is regarded as first line treatment, but only 15-25% of women will be completely cured. Approximately 65% will report that their condition improved, but long term adherence to treatment is problematic. In addition, at longer term (2-15 years) follow-up 30-50% of patients will end up having surgery. From 1996 a minimal invasive surgical procedure, the Tension-free Vaginal Tape (TVT) has rapidly become the gold standard in surgical treatment of stress urinary incontinence. With TVT 65-95% of women are cured. However, approximately 3-6% of women will develop symptoms of an overactive bladder, resulting in reduced quality of life. Because of its efficacy the TVT appears to be preferable over PFMT but both treatments and their costs have not been compared head-to-head in a randomised clinical trial.

**Methods/Design:**

A multi-centre randomised controlled trial will be performed for women between 35 - 80 years old with moderate to severe, predominantly stress, urinary incontinence, who have not received specialised PFMT or previous anti-incontinence surgery. Women will be assigned to either PFMT by a specialised physiotherapist for a standard of 9-18 session in a period of 6 months, or TVT(O) surgery. The main endpoint of the study is the subjective improvement of urinary incontinence. As secondary outcome the objective cure will be assessed from history and clinical parameters. Subjective improvement in quality of life will be measured by generic (EQ-5D) and disease-specific (Urinary Distress Inventory and Incontinence Impact Questionnaire) quality of life instruments. The economical endpoint is short term (1 year) incremental cost-effectiveness in terms of costs per additional year free of urinary incontinence and costs per Quality Adjusted Life Years (QALY) gained. Finally, treatment strategy and patient characteristics will be combined in a prediction model, to allow for individual treatment decisions in future patients. Four hundred female patients will be recruited from over 30 hospitals in the Netherlands

**Trial registration:**

Nederlands trial register: NTR 1248

## Background

Urinary incontinence is a common problem among adult women, with an estimated overall prevalence of 40% and between 6-10% of women with severe incontinence.[1] Stress urinary incontinence is the predominant type of incontinence affecting approximately 50% of incontinent women. Thus, 20% of adult women will experience stress urinary incontinence. The severity of urinary incontinence is often expressed in the number of incontinence episodes/week, where 7-14 episodes/week is considered as moderate and more than 14 episodes/week as severe incontinence.[1]

In addition, urinary incontinence is known to have a negative impact on quality of life and the economical costs related to it are substantial. These patient-centred and economical outcomes are important. For the treatment of stress urinary incontinence there are two options: pelvic floor muscle training (PFMT) and surgery. PFMT is currently advised as primary treatment, because it is statistically significant more likely to improve incontinence symptoms as compared to no or sham physiotherapy (OR 1.42, 95%CI 1.28-1.58).[2] Approximately 65% of women treated with PFMT experience improvement of their incontinence. However, a 100% cure rate (no incontinence episodes) is recorded in only 15 to 28% of women.[3,4] In addition to the low percentage of objective cure, the long-term efficacy of PFMT is under debate. After a 3-15 year follow-up, 25-50% of women primarily treated with PFMT have undergone surgery.[5-7] This can be due to lack of persistent efficacy, but may also be related to lack of compliance with the physiotherapy program.

In the past decade, surgery for stress incontinence has made a huge progression with the introduction of minimally invasive surgical techniques. The Tension-free Vaginal Tape (TVT) and Tension-free Vaginal Tape Obturator (TVT-O) are the most frequently performed procedures. In both cases, a small incision is made under the mid urethra through which a polypropylene mesh is placed without tension under the urethra. If abdominal pressure increases, the urethra is compressed to the tape and continence is restored. An advantage of these procedures is that they can be performed in day-care.[8] After a TVT(O) procedure approximately 66% of women are completely cured (100% dry) and 80-95% of women show an improvement.[9] Furthermore, this effect seems to be longstanding. However, although minimal invasive, stress incontinence surgery carries a risk of complications. Major complications are extremely rare with an incidence of 0.007% for bowel perforation and 0.012% for vascular injury.[8] The most common complication of bladder perforation during the procedure (approximately 3-6% for TVT and below 1% for TVT-O is easily recognized during the procedure itself and carries no long-term morbidity. Adverse outcome of surgery in terms of the development of new symptoms may be a bigger concern. Voiding difficulties and symptoms of an overactive bladder are reported in 6% of cases.[9]

In the Netherlands, women are usually seen by the general practitioner (GP) first. The GP Dutch guidelines (revised version 2006) on stress incontinence advocate to either start treatment with PFMT with instructions of the GP, or to refer to a specialised physiotherapist. In 2001 the Health Counsel reported that only 1.6% of women were referred to a physiotherapist.[10] Thus, the majority of incontinent women were not referred to specialised therapy. Treatment by the GP consists of giving verbal and written instructions (as is described in their guideline) how to contract and train the pelvic floor, with first revision after 3 months. This is clearly different from the weekly, individual sessions given by a specialised (biofeedback) physiotherapist. If treatment by the GP fails, it is advocated to refer the woman for specialised PFMT physiotherapy. This is the group of women where our study aims at.

The main objective of our study is to answer the question whether it is more (cost) effective to refer for specialised PFMT or for TVT(O) surgery after the standard initial instruction and training given by the GP has failed.

Primary surgery in this group of patients may be cost-effective when compared to PFMT as its cure rate is higher. A comparison of both strategies has been performed in a small sample of patients comparing abdominal Burch surgical procedure versus PFMT.[11] Although this single study concluded that primary surgery was preferable, the design and power did not meet the standards to provide sufficient scientific evidence. Finally, it is unclear which factors are associated with success or failure of PFMT and TVT. After identification of these factors a prediction model can be built that can further individualize treatment. In addition to our cost-effectiveness analyses we aim to develop such a prediction model.

## Methods

### Study Aims

The primary aim of the PORTRET study is to compare the clinical and cost-effectiveness of PFMT versus the TVT/TVT-O procedure as treatment for moderate to severe stress urinary incontinence.

### Study design and setting

The PORTRET study is a multidisciplinary, multicentre non-blinded therapeutic randomised controlled trial. Randomisation will be performed centrally with computerised randomisation tables. The two trial arms are PFMT by a specialised physiotherapist and a surgical intervention with the TVT or TVT-O. Recent data show that both the TVT and TVT-O are equally effective.[12,13] For obvious reasons blinding of treatment between PFMT and surgery will not be possible. To reflect daily practice as close as possible the assessment of costs will start directly after randomisation. We expect that the maximum effect of PFMT will be reached within 3-6 months. To account for possible changes in symptoms and changes in costs during this period, cost and symptom assessments are made every two months by means of a telephone administered questionnaire during the first 4 months. After that an assessment at 6, 12 and 18 months is performed. From literature, one of the predictive factors for the efficacy of treatment is the severity of incontinence at baseline. Therefore, we will introduce stratification by severity into the randomisation. We will stratify according to the severity (moderate or severe) as established by the Sandvik index [see table 1]. [14] The flowchart and study design are presented in figure 1 and table 2

**Figure 1 F1:**
[figure not shown]
**Flow chart**.

**Table 1 T1:** Sandvik Index

**SANDVIK INDEX**	Quantity of urine loss	
	
	1 = drops	2 = more than drops
Episodes		

1 = < 1 time a month	1	2

2 = 1 to more times a month	2	4

3 = 1 to more times a week	3	6

4 = daily	4	8

**Table 2 T2:** Study Design Schedule

	Baseline visit	Randomisation	study entry	2, 4 months*	6 months visit	12 months visit	18 months visit
Patient characteristics	X	**Checking Inclusion & Exclusion Criteria**					
		
**Gynaecologic examination**	**X**					**X**	
		
Assessment of pelvic floor functioning	X				X	X	
		
**48 hour bladder diary**	**X**				**X**	**X**	
		
Flow	X				X	X	
		
**Residual volume**	**X**				**X**	**X**	
		
Stress test	X				X	X	
		
**Sandvik index**	**X**				**X**	**X**	
		
24 hour pad test	X					X	
		
**Global Impression of severity**	**X**			**X**	**X**	**X**	**X**
		
Global Impression of improvement				X	X	X	X
		
**EQ-5D**			**X**		**X**	**X**	**X**
		
UDI	X				X	X	X
		
**IIQ**	**X**				**X**	**X**	**X**
		
Costs assessment*			X	X	X	X	X
		
**Compliance with treatment #**				**X**		**X**	
		
Complications of surgery#				X			

* After randomisation costs assessment will be made for both groups at 2 and 4 months in order to account for changes

occurring during progression of (PFMT) treatment.

# Compliance is measured only for the PFMT group in order to assure proper training, complications are only related to surgery.

### Ethical consideration

The study has been approved for by the medical ethical review commission of the Universitary Medical Centre Utrecht (METC UMCU 07/278). Full medical ethical approval has been obtained on 05-02-2008.

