### Study Interventions

After obtaining informed consent, eligible women will be assigned to either PFMT by a specialised physiotherapist for a standard of 9-18 sessions in a period of 6 months, or TVT(O) surgery.

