### Patient follow-up procedures

Patients will be followed from the start of primary therapy until 18 months later. Follow up will consist of various elements

In all patients the next items will be recorded at inclusion:

1. Baseline characteristics

2. History and clinical examination

3. 48 h-bladder (voiding and incontinence) diary

4. 24 h-padtest

5. Validated Quality of Life questionnaires (Urinary Distress Inventory, Incontinence Impact Questionnaire, Euroqol 5D, patient global impression of severity/improvement)

6. Uroflow measurement including post void residual volume

7. Cost-analysis questionnaire

The onset of primary therapy, either TVT(O) in the surgery arm of the study or PFMT in the physiotherapy arm of the study will be T = 0

In case of surgery, the patient will receive the standard care associated with the pre-, per- and postoperative standards of the participating hospital. She will visit the hospital after surgery at 6 weeks, 6, 12 and 18 months. Questionnaires will be handed out at these visits containing the items mentioned above. Furthermore, special attention will be given with respect to extra visits to the general practioner, physiotherapist or specialist visits in relation to the surgical procedure that might have taken place and physical examination will be performed. Costs associated with incontinence and therapy will also be assessed with telephone administered questionnaire at 2 and 4 months follow-up. Women who are enrolled for PFMT will be followed-up according to the same schedule besides the 6 weeks post operative check-up.

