### Patient outcome measures

This study will compare the clinical and cost-effectiveness of PFMT versus the TVT/TVT-O procedure as treatment for moderate to severe stress urinary incontinence.

Primary outcome: Subjective improvement of urinary incontinence

Secondary outcome(s):

1. Complete cure on objective and subjective parameters.

2. Subjective improvement in generic and disease-specific quality of life.

3. Complications and de novo urogenital symptoms.

4. The incremental cost-effectiveness of TVT as compared to PFMT, accounting for direct and indirect costs parameters.

5. Development of a prediction model for successful treatment, with the therapy given (PFMT or TVT) as independent variable in the model.

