### Statistical analysis

Data will be presented as numbers (percentage) for nominal variables or means (standard deviation) for interval variables. Differences between the two interventions will be analysed based on intention-to-treat analysis. For interval variables, differences between the two groups will be analysed with a Students t-test, proportions will be compared using the Chi-square test.

Multivariate logistic regression analysis will be used for the development of the prediction of successful treatment only. In literature, a wide range of patient characteristics were considered to be associated with the outcome of PFMT. In the Consultation on Incontinence (ICI) proceedings it was concluded that there are no reliable factors identified yet, because the number of observations and studies is too low.[2] However, several factors have been identified as possible predictors of a successful outcome after PFMT. To provide information on treatment effectiveness in different subgroups of patients participating in this trial, we will derive a prediction model and estimate interaction of treatment effect with baseline incontinence severity (number of leaks/week), duration of symptoms, increasing parity, Body Mass Index, baseline pelvic floor contraction ability, and treatment modality as factors.[2] The defined prediction model will therefore be pre-specified resulting in less over-optimism than models in which the choice of predictors is strongly driven by the data-set and the need for external validation.[19] From the multivariate logistic model, in which success will be defined as cure (no objective or subjective incontinence) at 12 and 18 months follow-up, we will estimate the weight of the different coefficients. The modelling process will be internally validated by bootstrap resampling. This technique gives an impression of how "over-optimistic" the model is i.e., how much the performance of the model may deteriorate when applied to a new group of similar patients.[20]

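### Surgery after a course of pelvic floor training has no scheduled complication assessment, so operative harm in the PFMT arm can be under-recorded

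*Protocol article*

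**What the plan says.** All references are to the protocol article.

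- **Outcome.** Under Patient outcome measures, the third secondary outcome is "Complications and de novo urogenital symptoms", with no restriction to one arm.
- **Analysis.** Under Statistical analysis: "Differences between the two interventions will be analysed based on intention-to-treat analysis".
- **Schedule.** In Table 2 the row "Complications of surgery" has one mark, in the column for 2 and 4 months. Nothing is marked at 6, 12 or 18 months.
- **Footnote to Table 2.** "Compliance is measured only for the PFMT group in order to assure proper training, complications are only related to surgery".
- **Clock.** Patient follow-up procedures fixes time zero at the start of treatment in each arm, in a sentence that begins "The onset of primary therapy, either TVT(O) in the surgery arm of the study or PFMT in the physiotherapy arm of the study will be".
- **Length of PFMT.** Study Interventions: "PFMT by a specialised physiotherapist for a standard of 9-18 sessions in a period of 6 months, or TVT(O) surgery".
- **Visits in the PFMT arm.** Patient follow-up procedures: "Women who are enrolled for PFMT will be followed-up according to the same schedule besides the 6 weeks post operative check-up".
- **Later surgery.** Background reports that, at 3-15 years, "25-50% of women primarily treated with PFMT have undergone surgery". The Abstract gives 30-50% at 2-15 years. Neither is an 18-month figure.

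**The concern.** The article expects some PFMT women to go on to surgery. Under intention to treat, what follows those operations belongs to the PFMT arm. Table 2 collects the global impression of improvement, EQ-5D, UDI, IIQ and costs to 18 months without limiting those rows by arm, so the benefit and the cost of a later operation enter that arm's results. The complications row stops at 4 months, before a full PFMT course has ended, and the 6-week post-operative check is left out for women allocated to PFMT.

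At stake is an uneven ledger. The PFMT-first strategy could be credited with the benefit of later operations without all of their operative harm, and the trial could lose operative safety data on some of the tapes it places.

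**Working it through.** **1. The plan's own figure.** The article states no figure for complications or crossover. Its only relevant number is 200 women per arm, from 65% versus 80% improvement, power 0.9 and alpha 0.05. With the two-sided normal formula and pooled variance under the null:

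- n = [1.960 × √(2 × 0.725 × 0.275) + 1.282 × √(0.65 × 0.35 + 0.80 × 0.20)]² / 0.15², which gives 185 per arm.
- With continuity correction it gives 198 per arm.

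So 200 is reproduced to within rounding. It serves below only as the denominator; the point does not depend on it.

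**2. The calendar.**

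| Event | Months from start of primary therapy |
|---|---|
| Scheduled complication assessments | 2 and 4 |
| End of the PFMT period | 6 |
| Later visits (no complications mark) | 6, 12, 18 |

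An operation after a full course comes after month 6, so no scheduled complication assessment follows it. This holds however the footnote is read. Counting from randomisation would not help, since therapy cannot start before randomisation. A woman who left training early and was operated on before month 4 could still be covered, if the row applies to her.

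**3. What other measurements pick up.** For both arms Table 2 has the UDI at 6, 12 and 18 months, flow and residual volume at 6 and 12 months, gynaecologic examination at 12 months, and costs to 18 months. Voiding difficulty and overactive-bladder symptoms, which Background puts at 6% of cases, are therefore largely observable after a later operation. Operative events are not: Background says bladder perforation is recognised during the procedure and has no long-term morbidity, so a later questionnaire or examination would not be expected to reveal it.

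**4. Size if operative events in later operations go unrecorded.** Let r be the complication rate per operation, taken as equal in primary and later operations, and c the share of PFMT women operated on within 18 months.

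- Recorded difference, surgery minus PFMT: r − 0 = r
- True intention-to-treat difference: r − c × r
- Overstatement against surgery: c × r

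Inputs: r = 3-6% is the Background range for bladder perforation with TVT. The range c = 10-50% is an **assumption**, because the article gives no 18-month rate. The surgery arm has 200 × r = 6 or 12 events.

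| c | r | PFMT events (200 × c × r) | Recorded difference, points | True difference, points | Overstated by, points |
|---|---|---|---|---|---|
| 10% | 3% | 0.6 | 3.0 | 2.7 | 0.3 |
| 10% | 6% | 1.2 | 6.0 | 5.4 | 0.6 |
| 25% | 3% | 1.5 | 3.0 | 2.25 | 0.75 |
| 25% | 6% | 3.0 | 6.0 | 4.5 | 1.5 |
| 50% | 3% | 3.0 | 3.0 | 1.5 | 1.5 |
| 50% | 6% | 6.0 | 6.0 | 3.0 | 3.0 |

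For TVT-O, Background gives perforation below 1%. The overstatement for that event is then below 0.1 points (0.10 × 1%) to below 0.5 points (0.50 × 1%).

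**The case against.** The strongest reply is that the footnote names an event and not an arm. It confines compliance to PFMT women but says only that complications relate to surgery, and the table row is worded the same way. An operation on a woman allocated to PFMT is surgery, so the row could cover her. **This stands.** A reader might infer that complications are by rule collected in the surgery arm alone; the contrast within the footnote and the omitted 6-week check suggest that, but the text does not state it. The calendar gap remains on either reading.

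Second, surgical patients also have visits at 6 weeks and at 6, 12 and 18 months, with attention to extra consultations related to the procedure and a physical examination. PFMT women share that schedule apart from the 6-week check, and most rows of Table 2 apply to both arms. **This stands in large part.** A reader might infer that later operations leave no complication record at all, or that the PFMT arm must show zero complications. Neither follows, because new urinary symptoms are largely captured and cost questionnaires may reveal the operation. The attention to extra visits, however, is written for women having surgery and concerns consultations, not operative events.

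Third, this is a condensed article, the case record forms are not at hand, and they may record later operations properly. **This limits the claim but does not remove it.** The article does not merely leave the matter open: it prints a schedule that ends before the operations in question can occur.

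Fourth, the sizes are modest. Crossover within 18 months is assumed, and perforation is a complication that the article itself regards as having no lasting effect. **This stands.** In every row of the table the surgery arm still has more events than the PFMT arm, so the direction of the comparison does not change.

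**Conclusion.** The point holds in a limited form. As printed, the schedule has no complication assessment for incontinence surgery performed after a PFMT course, although complications are a secondary outcome and differences are to be analysed by intention to treat. Operative and perioperative events are what can be missed.

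If they are missed, the error favours PFMT and equals c × r: about 0.3 to 3.0 percentage points over the assumed ranges, and less where TVT-O is used. The upper end needs half of the PFMT women to be operated on within 18 months, a share the article reports only as the top of its range at much longer follow-up. The calculation also assumes that primary and later operations have the same complication rate and that none of the later events is captured elsewhere.

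It would go too far to say that the harm comparison **is** biased. It **can** be, depending on how many women cross over and on recording practice in documents not at hand. The change is still worth making, because operative details not noted at the time are hard to recover reliably afterwards.

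**What to change.** 1. Reword the complications row of Table 2 and its footnote so that complications of any incontinence operation, in either arm, are recorded on the same form, with the collection window counted from the date of that operation through 18 months.
2. At the existing contacts in both arms, ask whether the woman has had incontinence surgery, and when.
3. Report complications by allocated arm and, separately, per operation performed.

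Lengthening the window for the surgery arm alone would not close the gap, since the women concerned were allocated to PFMT. The change affects data collection and reporting only. Its cost is one reworded row and footnote, one question at contacts that already take place, and slightly more data entry for women operated on later.
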